# Effects of Jianpi Lishi Jiedu granules on colorectal adenoma patients after endoscopic treatment: study protocol for a randomized, double-blinded, placebo-controlled clinical trial

**DOI:** 10.1186/s13063-022-06236-6

**Published:** 2022-04-23

**Keywords:** Jianpi Lishi Jiedu granules, Colorectal adenomas, Recurrence, Clinical efficacy, Randomized controlled trial, Study protocol

## Abstract

**Background:**

Colorectal adenomas (CRAs) are precancerous lesions of the large intestine presenting as colorectal polyps. At present, the conventional treatment methods for CRA mainly include high-frequency electrocoagulation and electroexcision, biopsy forceps polypectomy, cauterization by laser and microwave, and other endoscopic interventions. The principal advantages conferred by these treatment strategies include less trauma, quick postoperative recovery, and simplicity to perform. However, the higher recurrence rates and insignificant improvement of postoperative symptoms after endoscopic surgery are considerable drawbacks to this approach. Besides, there is currently no effective pharmacotherapy to prevent the recurrence of CRA. Jianpi Lishi Jiedu (JLJ) granules are a form of traditional Chinese medicine (TCM) used to manage postoperative patients with CRA, which has shown a certain degree of efficacy in clinical practice. However, its effectiveness and safety profile have not been convincingly evaluated. The purpose of this study is to evaluate the clinical efficacy and safety profile of JLJ granules in the management of postoperative patients with CRA and to observe the recurrence rate of adenoma in these patients.

**Methods:**

A randomized, double-blind, and placebo-controlled clinical trial is performed in this study. A total of 80 postoperative patients with CRA will be randomly classified into the Jianpi Lishi Jiedu granules group or the placebo control group. Patients in both groups shall receive 3 months of intervention, after which medical follow-up and safety evaluation will be performed for all of the patients. The primary outcome is the recurrence rate of adenomas within 12 months. The secondary outcomes are the cardinal TCM symptom scores, minor TCM symptom scores, Bristol Stool Scale, efficacy of TCM symptoms, safety indicators, and blinding assessment.

**Discussion:**

In this study, the impact on the recurrence of adenomas and the efficacy and safety of JLJ granules in terms of improving the clinical symptoms of postoperative patients with CRA will be evaluated.

**Trial registration:**

Trial registration Chinese Clinical Trial Registry ChiCTR 2100044297. Registered on March 16, 2021

**Supplementary Information:**

The online version contains supplementary material available at 10.1186/s13063-022-06236-6.

Most patients with CRA would not display specific symptoms, and frequent colonoscopy screenings would cause a huge economic burden to patients. Besides, there is currently no reliable treatment plan or measure to prevent recurrence for post-surgical CRA patients. The focus of most clinical studies is non-steroidal anti-inflammatory drugs (NSAIDs), such as aspirin, sulindac, and celecoxib [10, 11]. There are also some studies on other drugs such as beneficial intestinal bacteria preparations [12–14], but their clinical application value remains debatable, and they have not been widely recognized and applied. Thus, clinicians and surgeons face the immense challenge of developing safe and effective drugs for symptomatic relief in postoperative CRA patients, as well as preventing recurrence and avoiding canceration.

Over the recent years, with the in-depth research carried on TCM, people are increasingly aware of its unique advantages in the prevention and treatment of CRA [15, 16]. Our team found that in clinical practice, Jianpi Lishi Jiedu granules developed from a classic Chinese herbal medicine formula can not only relieve the symptoms of patients with CRA after endoscopic treatment, but also reduce the recurrence rate of adenoma [17]. However, its exact clinical efficacy, mechanism of influence on the recurrence of adenomas, and safety profile have not been convincingly evaluated. Therefore, this protocol, a randomized, double-blinded, and placebo-controlled trial, has been designed in this study to further clarify the clinical efficacy of the Jianpi Lishi Jiedu recipe in patients with CRA after endoscopic surgery, observe the recurrence rate of adenomas, and evaluate its safety profile.

## Methods/design

### Study design

This study presents a randomized, double-blinded, and placebo-controlled clinical trial performed in accordance with the Declaration of Helsinki, the Standard Protocol Items: Recommendations for Interventional Trials (SPIRIT) 2013 Statement [18], and the Standard Protocol Items for Clinical Trials with Traditional Chinese Medicine: Recommendations, Explanation and Elaboration (SPIRIT-TCM) Extension 2018 Statement [19] from June 2021 to June 2023. In this study, a total of 80 eligible patients will be enrolled and randomly classified into the JLJ granules group or the placebo control group. All the patients voluntarily will sign an informed consent before being included. Each included patient will be numbered in sequence and randomly classified into two groups using a ratio of 1:1. Participants in the JLJ granules group will be instructed to take JLJ granules (110 g per day) for 3 consecutive months, while participants in the placebo control group will be given placebo granules with the same appearance and smell as JLJ granules but no therapeutic effect (110 g per day) for 3 consecutive months. All of the researchers and patients will be blinded right from the beginning of the trial. All the clinical data will be recorded before the intervention (0 week) and after the intervention (at month 3, month 6, and month 12), and the results of the electronic colonoscopy will be recorded at month 12. The proposed project schedule is illustrated as a flowchart in Figs. 1 and 2.

**Fig. 1 Fig1:**
[figure not shown]
The flowchart of the protocol

**Fig. 2 Fig2:**
[figure not shown]
The proposed project schedule

### Objective and hypothesis

This study’s principal objective is to assess the recurrence of CRA, conduct an evaluation of the clinical efficacy of JLJ granules in the treatment of postoperative patients with CRA, and explore the safety profile of JLJ granules in the treatment of postoperative patients with CRA. In this study protocol, it will be assumed that, compared with the placebo, JLJ granules have better effects in terms of the recurrence rate of CRA, major symptom alleviation, the remission rate of minor symptoms, the Bristol stool scale, and the efficacy for patients with CRA after surgery, with no significant adverse effects despite an adequate safety profile.

### Participants

In this study, patients will be recruited in the outpatient department, Department of Gastroenterology and gastrointestinal endoscopy center of Nanjing Integrated Traditional Chinese And Western Medicine Hospital, and diagnosed according to the results of electronic colonoscopy and histopathology. All of the 80 patients included must voluntarily sign an informed consent. Data collection will be performed by two professionally trained researchers to ensure that the data is relatively objective and accurate.

### Inclusion criteria

Patients diagnosed with colorectal polyps through colonoscopy and adenoma through histopathological examination and received resection of the adenoma with biopsy clips or endoscopic resection within 4 weeks, including snare polypectomy (SS), endoscopic mucosal resection (EMR), piecemeal EMR (pEMR), endoscopic submucosal dissection (ESD), etc.Patients with TCM syndromes of spleen-asthenia with excessive damp; refer to “Guidance principle of clinical study on new drug of traditional Chinese medicine” [20]. The clinical symptoms of spleen-asthenia with excessive damp are stated in Table 1. The cardinal symptoms in line with 2 items and the minor symptoms in line with 1 item shall be diagnosed as spleen-asthenia with excessive dampPatients with age ranging from 18 to 65 years old, regardless of genderPatients that voluntarily accepted observation and signed the informed consent and ethical principles

**Table 1 Tab1:** The scores of TCM syndrome

Symptoms	Scores of TCM symptoms			
	None	Mild	Moderate	Severe
	0	1	2	3
**Cardinal TCM symptom**				
Diarrhea or mucus	None	Diarrhea or mucus, defecate 3–4 times/day	Diarrhea or mucus, defecate 5–10 times/day	Diarrhea or mucus, defecate>10 times/day
Constipation	None	Dry stool, defecate 1 time/day	Dry stool, defecate once/2–3 days	Very dry stool, defecate once/5–7 days
Abdominal pain	None	Occasionally, mild abdominal pain	Sometimes, moderate abdominal pain	Often, severe abdominal pain
Abdominal distension	None	Occasionally, mild abdominal distension	Sometimes, moderate abdominal distension	Often, severe abdominal distension
Inappetence	None	Mild, less than 1/3 reduction in food intake	Moderate, more than 1/3 reduction in food intake	Severe, no eating all day long
Dry or sticky feeling in the mouth	None	Mild, occasionally	Moderate, sometimes	Severe, often
**Minor TCM symptom**				
Fatigue	None	Mild, be able to insist on light physical work	Moderate, barely stick to daily activities	Severe, inactive all day
Bowel sound	None	Mild, occasionally	Moderate, sometimes	Severe, often
Nausea or vomiting	None	Mild, occasionally	Moderate, sometimes	Severe, often
Tongue and pulse:				

### Exclusion criteria

Patients not falling under the diagnostic criteria for colorectal polyps or with pathologies not considered within the diagnostic criteria for adenoma or TCM syndromes of spleen-asthenia with excessive dampPregnant or lactating women or those preparing to have childrenPatients with an allergic constitution or an allergy to multiple drugs, drug addicts, and alcoholicsPatients with comorbidities such as serious cardiovascular, pulmonary, hepatic, renal, and hematologic diseasesPatients suspected of canceration or in whom canceration has been confirmed by biopsyPatients taking drugs or undergoing other clinical trials within 1 monthPatients with severe physical disabilities (such as deafness, blindness, intellectual disability, mental disability, etc.) who are unable to cooperate or unwilling to cooperate

### Withdrawal criteria/dropout criteria/termination criteria

Patients not in line with the aforementioned inclusion criteriaPatients with incomplete clinical data, lost during medical follow-up, or requested to be withdrawn from the trialPatients who requested to be withdrawn from the trial, patients with poor compliance or not following the drug administration protocol or with a change in the test drugs or administration of banned drugsPatients with serious changes in the disease course or complications during the trialPatients with serious adverse events during the trial, resulting in the inability to continue the trial

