### Allocation concealment and blinding

The drug administrator will number the outer packages of drug packaging based on a random numerical sequence table. The independent statistician will prepare the allocation sequence table based on the above randomization and random numerical table, encrypt the computer software, and make 3 copies. Said copies will be kept by the independent statistician, the trial designer, and the drug administrator, respectively. The random numerical table, allocation sequence table, and numbers selected by relevant patients will be sealed in opaque envelopes. Before the trial completion, the group allocations will be masked, and all the patients, clinicians, nurses, data managers, statisticians, and other personnel will be blinded to the trial, and the random sequence table and number must be kept strictly confidential. The blinding can only be uncovered with the consent of the main researchers after completion of the trial and data analysis or in case an emergently severe adverse event occurs. Placebo and JLJ granules will be both packed in opaque packages, which will be exactly the same in appearance, color, smell, taste, dosage, and packaging. For emergency unblinding during the study, relevant cases will be considered as dropped out.

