### Sample size

The sample size is estimated to the recurrence rate of CRAs as the primary outcome of the trial; test level: *α* = 0.05, test efficacy: 1−*β*; 1−*β* = 0.9, so *β* = 0.1. Take *α* = 0.05 (bilateral), *β* = 0.1, *Z*_*α*/2_ = *Z*_0.05/2_ = 1.96, and *Z*_0.10_ = 1.282, the sample size of the treatment group and the control group each account for 50%, thus, Q1 = Q2 = 0.5. As per the previous literature [22], we assumed that the recurrence rate of adenomas of the TCM treatment group is about 20% (p1 ≈ 0.2), and the recurrence rate of the placebo control group is roughly 35% (p2 ≈ 0.35). We use the PASW(V.18.0) software; as per the two sample rate calculation formula: *n* = ((*Z*_*α*/2_√ (p(1−p)(Q1^−1^ + Q2^−1^)) + *Z*_*β*_√((p_1_(1−p_1_)/Q_1_) + (p_2_ (1−p_2_)/Q_2_))/(p_1_−p_2_))^2^, we can conclude that *n* ≈ 66. Taking into account patients’ withdrawal and loss during follow-up, we also assumed that the dropout rate in each group will be 15%, implying that *n* = 80, namely 40 cases in the treatment group and the control group, respectively.

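### One withdrawal list merges stopping the granules with leaving the trial, so month-12 primary outcomes that could still be measured may be lost

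*Protocol article*

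**What the plan says.** The section on withdrawal, dropout and termination criteria in the protocol article is a single list. It names failure to meet the inclusion criteria, incomplete clinical data, loss to follow-up and the patient's own request. It also names "patients with poor compliance or not following the drug administration protocol", with change of test drug and use of banned drugs alongside. It ends with serious changes in the disease course or complications, and with serious adverse events, the last only where the patient cannot continue. Nothing in it distinguishes a patient who stops the granules from one who leaves the trial.

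The section on allocation concealment and blinding adds: "For emergency unblinding during the study, relevant cases will be considered as dropped out".

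Under Study design and Study period, treatment lasts 3 months, visits are at months 3, 6 and 12, and the repeat colonoscopy is at month 12. Under Primary outcome, recurrence within 12 months is divided by the number of patients in the group (intra-group patients), and the article does not say whether that means all randomised. Under Statistical analysis, rates are compared by a chi-square test. Under Sample size, the total is raised from 66 to 80, with the reason "Taking into account patients’ withdrawal and loss during follow-up".

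**The concern.** Most reasons on the list arise after randomisation. Compliance, tolerability, use of other drugs and disease course can each depend on the treatment received, or be linked to the outcome. If such patients leave the trial, the month-12 comparison is between those who remained, and randomisation no longer protects it.

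The timing makes the loss avoidable. A patient who stops taking granules in month 2 is withdrawn ten months before the primary reading, although a colonoscopy at month 12 would still show whether an adenoma had recurred. No section says that withdrawn or unblinded patients still have it. An analysis plan written later can define an analysis set, but it cannot recover a colonoscopy that was never done. With 40 patients per arm, a few selectively missing results can shift the observed difference by several points.

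**Working it through.** **The plan's own figures.** The dropout step roughly reproduces: 66/(1 − 0.15) = 77.6, so 78, which the plan takes to 80. At 40 per arm, 15% is 0.15 × 40 = 6 patients, leaving 34. The 66 itself does not follow from the stated formula: with p = 0.275, ((1.96 × √(0.275 × 0.725 × 4) + 1.282 × √(0.2 × 0.8/0.5 + 0.35 × 0.65/0.5))/0.15)² = ((1.750 + 1.129)/0.15)² = 368.4 in total. That is a separate matter, and nothing below depends on it.

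**Inputs for the illustration.**
- Placebo recurrence: "the recurrence rate of the placebo control group is roughly 35% (p2 ≈ 0.35"), from Sample size. With no true effect, both arms have 0.35 × 40 = 14 recurrences.
- Number removed: 6 of 40, taken from "the dropout rate in each group will be 15"%. This is an assumption, because the article ties the 15% to withdrawal and loss, not to each reason on the list.
- Planned difference: 35% − 20% = 15 points.
- How many of those removed would have recurred (k): not in the document, so a range is shown.

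**Removal in the JLJ arm only.** Observed JLJ rate = (14 − k)/34. Placebo stays at 14/40 = 35.0%.

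| k of 6 | JLJ observed | False benefit of JLJ (points) |
|---|---|---|
| 0 | 14/34 = 41.2% | −6.2 |
| 2 | 12/34 = 35.3% | −0.3 |
| 3 | 11/34 = 32.4% | 2.6 |
| 5 | 9/34 = 26.5% | 8.5 |
| 6 | 8/34 = 23.5% | 11.5 |

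If removal were unrelated to recurrence, k would be about 6 × 0.35 = 2.1, with almost no shift. All 6 being recurrences would then have probability C(14,6)/C(40,6) = 3,003/3,838,380, about 0.0008. The lower rows therefore describe selective removal, and the last is the extreme.

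**Removal of 6 in each arm.** With 2 recurrences among the 6 placebo removals, placebo is 12/34 = 35.3%. The false benefit is then 1/34 = 2.9 points at k = 3 and 4/34 = 11.8 points at k = 6.

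**Error rate.** A simulation (200,000 runs) took 35% recurrence in both arms, 40 per arm, an average of 15% removed per arm, and placebo removals unrelated to recurrence.

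| JLJ recurrences removed | JLJ non-recurrences removed | False benefit (points) | Two-sided type I error |
|---|---|---|---|
| 15% | 15% | 0 | 5.1% |
| 25% | 9.6% | about 4 | 6.7% |
| 30% | 6.9% | about 6 | 8.7% |
| 43% | 0% | about 11 | 18% |

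**The case against.** The strongest reply is that the article nowhere says withdrawn patients are excluded from the analysis. The denominator can be read as everyone allocated to the group, and analysis sets and missing-data handling are commonly left to an analysis plan, which is not at hand. That stands: a reader might infer that the plan fixes an analysis that is not intention-to-treat, and the document only implies it. It does not answer the point about follow-up, because who stays under observation is a protocol rule and the rule is written here.

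Other stronger readings also fail:
- **The 15% proves exclusion.** It does not. The stated reason is withdrawal and loss, and inflating for loss is routine in intention-to-treat trials too.
- **Safety follow-up ends after a serious adverse event.** The Adverse events section requires close follow-up of these patients, and the withdrawal list covers only events that prevent continuation. The two sections need reconciling, no more.
- **Primary events are discarded as serious disease change.** This is possible, since that term is undefined, but no colonoscopy is scheduled before month 12, and nothing says a recurrence triggers withdrawal. Canceration is outside the primary definition, which counts new adenomatous lesions.
- **An 11.5-point bias is to be expected.** That figure is a one-arm extreme. In a double-blind trial with matched placebo, nothing in the document points to strong outcome-related removal in one arm. Even 8/34 against 12/34 gives an uncorrected chi-square p of 0.29. The harm is a biased estimate and a raised error rate, not a guaranteed false positive.

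**Conclusion.** The concern holds in this form: the withdrawal list and the unblinding sentence treat departures from treatment as departures from the trial, and so give up month-12 results that could still be obtained, for reasons that may depend on treatment or outcome. Exclusion from the analysis is implied and left open by an undefined denominator.

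The document does not determine the size or direction of the bias. Assuming no true effect, 35% recurrence, and 6 of 40 removed from JLJ only, the false benefit is 2.6 points when half of those removed would have recurred and 11.5 points at the extreme. It is near zero when removal is unrelated to outcome, and reversed when those removed are mostly patients without recurrence. The design difference is 15 points, so moderate selection already matters. The article reports that the trial is enrolling, and colonoscopies missed under the current wording cannot be recovered afterwards.

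**What to change.** Amend the protocol as follows. None of this changes when or why granules are stopped.

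1. Split the list into reasons for stopping study granules and reasons for leaving follow-up.
2. Keep patients who stop granules, deviate or are unblinded in follow-up, with the month-12 colonoscopy already scheduled, unless they withdraw consent or cannot continue.
3. In the blinding section, replace the sentence that makes emergency-unblinded cases dropouts with one that retains them in follow-up and analysis.
4. Define the primary comparison as all randomised patients in their allocated arm. State a rule for missing month-12 colonoscopies, for example multiple imputation with a worst-case sensitivity analysis.
5. State that an adenoma recurrence found before month 12 counts as a primary event, in line with the 12-month window in the outcome definition.
6. Keep the compliant subset as a per-protocol sensitivity analysis.
7. Reconcile the withdrawal list with the Adverse events section on follow-up of serious adverse events.

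The cost is a short amendment and the effort of retaining patients who have stopped treatment. The colonoscopy is already on the schedule, although the article does not say it is funded for these patients and it reports funding constraints. Including non-compliers will dilute the estimated effect somewhat.

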### Randomization

In this clinical trial, 80 postoperative patients with CRA will be randomly distributed into a JLJ granule (treatment) group or the placebo control group in a ratio of 1:1, according to the randomized sequence table generated by SAS 9.4 (SAS Institute Inc, Cary, NC, USA), with each patient attributed a number ranging from 01 to 80; each of these codes is unique to a specific patient. The test designer will decide the number series for the JLJ granule group and the control group. JLJ granules and placebo granules will be numbered and labeled with the same serial numbers as described above. An independent statistician from a third-party statistical agency, the trial designer, and the drug administrator will participate in the randomization, but will not be involved in the study process and the statistical analysis of the test results.

### Allocation concealment and blinding

The drug administrator will number the outer packages of drug packaging based on a random numerical sequence table. The independent statistician will prepare the allocation sequence table based on the above randomization and random numerical table, encrypt the computer software, and make 3 copies. Said copies will be kept by the independent statistician, the trial designer, and the drug administrator, respectively. The random numerical table, allocation sequence table, and numbers selected by relevant patients will be sealed in opaque envelopes. Before the trial completion, the group allocations will be masked, and all the patients, clinicians, nurses, data managers, statisticians, and other personnel will be blinded to the trial, and the random sequence table and number must be kept strictly confidential. The blinding can only be uncovered with the consent of the main researchers after completion of the trial and data analysis or in case an emergently severe adverse event occurs. Placebo and JLJ granules will be both packed in opaque packages, which will be exactly the same in appearance, color, smell, taste, dosage, and packaging. For emergency unblinding during the study, relevant cases will be considered as dropped out.

